## Aim and hypothesis

### Primary exploratory aim: auditory-driven changes in body perception

The primary aim of this study is to gain an exploratory understanding of the influence on body perception of non-naturalistic auditory information in participants with subthreshold EDs symptomatology using two body illusions. The scarce literature on the topic precludes us from considering a confirmatory model. As a result, the following hypotheses are all descriptive–exploratory.

**Hypotheses 1 (H1)**: Participants with subthreshold ED symptomatology will differ from participants without ED symptomatology in their degree of body image distortion. This hypothesis is exploratory, as alternatively, both groups may show the same degree of distortion.

H1 is based on previous literature that has shown a conflicting set of results. While there is strong evidence to suggest that young females with ED symptomatology and individuals with EDs tend to overestimate their body size compared to control individuals, some evidence suggests that body image distortions are not specific to this population, implying that they can underestimate their body size [24] or even be as accurate as individuals without ED symptomatology [32].

**Hypotheses 2 (H2)**: Participants with subthreshold ED symptomatology will show stronger auditory-driven body illusions, compared to control individuals.

H2 is based on the traditional hypothesis in support of a stronger influence of external sensory signals, leading to stronger body illusions in people with and subthreshold EDs [15–17].

**Hypotheses 3 (H3)**: Participants with subthreshold ED symptomatology, as compared to without ED symptomatology, will present unusual patterns of results in the finger elongation or shrinking waist illusion, suggesting impairments in the integration of artificial auditory signals into their body image.

H3 hypothesizes that participants with subthreshold ED symptomatology, as compared to people without ED symptomatology, will present unusual patterns of results, that is, the perceived finger elongation or shrinking waist will not necessarily occur in the ascending pitch condition (or not only in that condition, as in [24]. The results will shed light on whether the alteration in the mechanisms integrating auditory signals into body image is present only to natural signals related to body weight/size (e.g., footsteps) or it is linked to any auditory signals.

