## Participants

The experiment will be conducted individually in a quiet laboratory room [see Additional file 1, section A]. In keeping with previous literature and to facilitate the comparison and interpretation of the results because of the variability shown in related measures, the sample will comprise young adult females (sex assigned at birth) in the 18–24 age range, where the prevalence of EDs in this population is the highest [34]. However, it should be pointed out that previous evidence has reported high prevalence of EDs not only in female samples but also in other populations such as in men or gender diverse individuals [35–37]. Additionally, we decided to focus on the waist because this body part has been shown to be particularly emotionally salient for females and a reliable indicator of body mass index (BMI) [4, 38]. Participants will be recruited through public advertisements and social media posts (convenience sampling) and they will be paid or compensated with grade points for their time. To split the sample into participants with and without ED symptomatology, the Spanish Eating Disorder Examination Questionnaire (S-EDE-Q) [39]) will be administered (see Table 1 for more details). The pre-screening will allow to form two groups of similar size: once the desired participant sample size has been reached for one of the groups, only participants falling into the other group defined for the study will be invited to take part. The S-EDE-Q have demonstrated good psychometric properties in young female adults in Spain [39]. A global EDE-Q score ≥ 2.8 has been shown to provide an optimal trade-off between sensitivity and specificity when it is used for screening in primary care [40]. Available resources for participants will include psychoeducation and support for body image and eating-related concerns, provided by a team member. The availability of these resources will be specified in the informed consent. Moreover, to not assume that all individuals are cis-gender, gender identity will be assessed through an additional question.

**Table 1 Tab1:** Overview of study measures and data collection timepoints

Measure	Description	Baseline	Experiment	
			1	2
Demographic data	Participants’ age. In addition, BMI will be calculated with the following formula: BMI = weight (kg)/(height (m)^2^) following the World Health Organization’s criterion [45]	X		
Information consent	Written informed consent	X		

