S-EDE-Q†	To assess body EDs psychopathology. Self-administered questionnaire composed of 28 items using 7-point Likert scales ranging from 0 (not at all) to 6 points (markedly) about the previous 28 days. Four subscales are measured, including: dietary restraint (5 items), shape concerns (8 items), weight concerns (5 items), and eating concerns (5 items). For each subscale, the score ranges from 0 and 6 points. Participants will be grouped according to a global index score which is the average of the four subscale scores. As in Mond et al. [36], we will use a cut-off point ≥ 2.8 as clinically significant. Higher scores indicating a higher ED pathology. The S-EDE-Q have shown adequate internal consistency (Cronbach’s alpha ≥ .81 for all subscales), acceptable sensitivity (≥ 0.95), specificity (≥ 0.90), and positive (≥ 0.59) and negative (≥ 0.99) predictive values, and positive and significant correlation (≥ 0.70) with EDE diagnoses	X		
HSPS‡	To assess the tendency to process stimuli and information more strongly and deeply than others (sensory-processing sensitivity). Self-administered questionnaire composed of 27 items using 7-point Likert scales ranging from 0 (not at all) to 6 points (markedly). Five subscales are measured including: (1) sensitivity to overstimulation (9 items); (2) aesthetic sensitivity (6 items); (3) low sensory threshold (5 items); (4) fine psychological discrimination (4 items); (5) harm avoidance (3 items). For each subscale, the score ranges from 27 to 189 points. Higher scores indicate higher sensitivity level. A total global score will be obtained by averaging the five subscales. The HSPS have shown adequate internal consistency (Cronbach’s alpha ≥ 0.81 for all subscales) and construct validity in the adult Spanish population	X		

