### Statistical analyses

#### Primary aim: auditory-driven changes in body perception Baseline measures

To determine differences between the groups, analyses will be performed with a Student's t-test paired comparison (for normal distribution) or Wilcoxon tests (for non-normal distribution) for ED symptomatology (EDE-Q), interoceptive body awareness (MAIA), sensory-processing sensitivity (HSPS) and body size discrepancy (Body visualizer tool).

#### Experiment 1 and Experiment 2

For the estimations of body part position/size, confidence task and items from the body feelings questionnaires we will follow a 2 × 3 ANOVA within-between interaction repeated-measures design (see Table 2). Specifically, we will use non-parametric ANOVAs on aligned rank (ART) data, suitable for ordinal data, using the R package ARTool [56]. The ANOVAs will involve a group factor with 2 levels (subthreshold EDs and controls) and a feedback condition factor with 3 levels (‘ascendent’, ‘constant’, ‘descendent’). Prior the analysis, assumptions of independence, normality and sphericity will be checked. As in [24], we will include the degree of body size discrepancy as covariate in case of significant baseline differences. Appropriate post-hoc tests will be conducted in case of significant differences.

**Table 2 Tab2:** ANOVA 2 × 3 design

Group	Feedback condition		
	Ascendent	Constant	Descendent
Subthreshold EDs	Subthreshold EDs–Ascendent	Subthreshold EDs–Constant	Subthreshold EDs–Descendent
Controls	Controls–Ascendent	Controls–Constant	Controls–Descendent

For body size discrepancy, we will follow a 2 × 3 ANOVA within-between interaction repeated-measures design (see Table 3). The ANOVAs will involve a group factor with 2 levels (subthreshold EDs and controls), a time factor with two levels (baseline and post-experiment) and a feedback condition factor with 3 levels (‘ascendent’, ‘constant’, ‘descendent’).

**Table 3 Tab3:** ANOVA 2 × 2 × 3 design

Group	Baseline	Experiment		
		Feedback condition		
		Ascendent	Constant	Descendent
Subthreshold EDs	Subthreshold EDs Baseline	Subthreshold EDs Post-experiment Ascendent	Subthreshold EDs Post-experiment Constant	Subthreshold EDs Post-experiment Descendent
Controls	Controls Baseline	Controls Post-experiment Ascendent	Controls Post-experiment Constant	Controls Post-experiment Descendent

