The degree of body size discrepancy as covariate will be included in case of significant baseline differences. Similarly, assumptions of independence, normality and sphericity will be checked and post-hoc tests will be conducted if appropriate.

Following a similar approach as in [24], the proposed analysis will be based on the division of the controls vs. sub threshold group based on scores falling above or below the cut off of 2.8 on the EDE-Q. A complementary, secondary correlational analysis will be performed between estimation of body position/size measures and EDE-Q scores considering the entire sample.

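### The planned full-scale use of the EDE-Q score does not test the tone response in H2 and H3; a named EDE-Q × tone analysis beside the 2.8-cut group ANOVA would

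*Protocol article*

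**What the plan says.** Every participant has a score on a continuous scale. Table 1 gives four subscales, each from 0 to 6, and says "Participants will be grouped according to a global index score which is the average of the four subscale scores". It adds "we will use a cut-off point ≥ 2.8 as clinically significant".

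Under Statistical analyses, the ANOVAs for both experiments have "a group factor with 2 levels (subthreshold EDs and controls) and a feedback condition factor with 3 levels". The text closing that section confirms that "the proposed analysis will be based on the division of the controls vs. sub threshold group based on scores falling above or below the cut", with the threshold set at 2.8, and says this follows an approach similar to reference 24, the earlier footstep-sound study.

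The full-scale score appears once in the analysis of the primary aim: "A complementary, secondary correlational analysis will be performed between estimation of body position/size measures and EDE-Q scores considering the entire sample". Under Data management, the position and size measures are 12 summary scores per participant: four measures (knuckle position, fingertip position, finger length, waist width) in each of three tone conditions. No difference between tones is defined there.

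On labels, Participants says: "To split the sample into participants with and without ED symptomatology, the Spanish Eating Disorder Examination Questionnaire (S-EDE-Q") is used. H1 reads "Participants with subthreshold ED symptomatology will differ from participants without ED symptomatology in their degree of body image distortion", and H2 to H4 are also worded as contrasts between two groups. The same section on participants supports the cut-off as a primary-care screening threshold, in a sentence that begins "A global EDE-Q score ≥ 2.8 has been shown to provide an optimal trade-off between sensitivity and specificity when it is used for screening in".

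**The concern.** H2 says the illusion is stronger in the symptomatic group. H3 says its pattern across tones is unusual. Both are statements about how an estimate changes from one tone to another. A correlation between EDE-Q and, for example, perceived waist width under the ascending tone mixes two things: a general tendency to over- or underestimate the body, which is closer to H1, and the response to the tone. A woman who overestimates her waist equally under all three tones contributes to that correlation without showing any illusion.

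The tone response is therefore tested only through the two-level factor. If it grows gradually with symptom level, a null group-by-tone result could partly reflect the cut, in a study that already concedes limited power. The planned correlation would not reveal this. It also covers only position and size estimates, not confidence, body feelings or body size discrepancy.

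A smaller point concerns the label. A control is any eligible woman below 2.8, with no lower limit or gap, so a score of 2.7 counts as being without symptomatology. The cut-off as described marks clinical significance, not absence of symptoms.

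**Working it through.** **The article's own benchmark.** No sample size was calculated, so there is no power figure to reproduce. Sample size considerations cites d = 0.4, power 0.80 and alpha 0.05 as the conventional standard.
- Required n per group = 2 × (1.960 + 0.842)² / 0.4² ≈ 98.1, so 99 (100 with the t distribution).
- With 50 per group, the noncentrality is 0.4 × √(50/2) = 2.0. On 98 df, two-sided, power is 0.508. This agrees with the article's caveat that power might not be sufficient.

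**Inputs for the comparison.** From the article: 50 + 50 women, d = 0.4, and at least 450 screened, which implies about 50/450 = 11.1% at or above 2.8. Assumed: the EDE-Q distribution (exponential, half-normal, normal, gamma and beta shapes), a two-sided test, and a one-degree-of-freedom tone contrast per woman analysed by t-test or Pearson correlation.

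**Information kept by the split.** In the quota sample, the group label correlates about 0.84 to 0.88 with the score. Squared, the efficiency RE is about 0.70 to 0.78.

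**Linear relation.** Group R² = (d/2)² / ((d/2)² + 1) = 0.04/1.04 = 0.0385. Score R² = group R² / RE. Noncentrality = √(100 × R² / (1 − R²)).
- RE = 0.70: R² = 0.0550, noncentrality 2.41, power 0.666.
- RE = 0.78: R² = 0.0493, noncentrality 2.28, power 0.616.

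Simulation gives 61–66% by score against about 51% by group.

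**Step at 2.8.** Score R² = group R² × RE.
- RE = 0.70: R² = 0.0269, noncentrality 1.66, power 0.377.
- RE = 0.78: R² = 0.0300, noncentrality 1.76, power 0.414.

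The score analysis now loses about 9–13 points; the simulations together give about 8–14.

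**Other effect sizes, linear relation (RE 0.70 to 0.78).**

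| d | By group | By score | Gain (points) |
|---|---|---|---|
| 0.2 | 0.168 | 0.220 to 0.202 | 5 to 3 |
| 0.3 | 0.318 | 0.430 to 0.393 | 11 to 8 |
| 0.4 | 0.508 | 0.666 to 0.616 | 16 to 11 |
| 0.5 | 0.697 | 0.851 to 0.807 | 15 to 11 |
| 0.57 | 0.806 | 0.930 to 0.898 | 12 to 9 |
| 0.8 | 0.977 | 0.998 to 0.996 | 2 |

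**Sensitivity to shape.** A gamma shape (k = 2) with 20% above the cut gives RE 0.66, a gain of 18 points under linearity and a loss of 14.5 under a step, both at d = 0.4. The figures depend on a distribution that the article does not give.

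**Controls near the cut.** With 11.1% above 2.8, the assumed gamma and normal shapes put about 7–12% of controls at 2.3–2.8 and 16–30% at 1.8–2.8. The label point does not depend on these shares.

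**The case against.** The two-group comparison is the design. Recruitment is by quota on the cut-off, H1 to H4 are group contrasts, and comparability with the footstep-sound study is a stated reason. A reader might infer that primary-care screening is the only ground for 2.8, or that the group ANOVA is an error. The article supports neither reading.

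The power calculation is also open to challenge. It models a t-test on one contrast, whereas the plan is an aligned-rank 2 × 3 ANOVA whose interaction has two degrees of freedom. The d of 0.4 is a convention, not a design value. Nothing in the article says the relation is a straight line; H3 expects unusual patterns, and the earlier study's result ran contrary to expectation. This stands: the figures are illustrative and conditional.

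A further argument is that the correlation could be read as including tone differences, because the secondary aim equates susceptibility to the illusions with body-image flexibility and then uses the position and size estimates as its measure. That reading is possible, but the measures are defined only per condition, so the sentence does not secure it. The analyses are written out here, so tightening that sentence does not ask for detail that an article usually leaves to a fuller plan.

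The article also declares the hypotheses exploratory and discloses limited power. That lowers the stakes, but a graded relation is the kind of pattern an exploratory study would want to see. The labelling point is largely wording, since the 2.8 rule is visible throughout.

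**Conclusion.** The concern holds in a limited form. The group ANOVA is sound for the question asked, but the companion analysis on the continuous score is aimed at the wrong quantity and, as written, leaves H2 and H3 untested on the full scale.

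A reader might infer that cutting the score simply costs 10 to 15 points of power. The documents do not support a flat figure. Under a roughly linear relation and the assumed EDE-Q shapes, the gain from using the score is about 10–15 points near d = 0.4 and about 2–16 points over d = 0.2 to 0.8. If the effect is a step at 2.8, the sign reverses and the group analysis is better by about 8–14 points at d = 0.4. Neither analysis dominates, which is the reason to report both. This is a cheap improvement, not a fault that undermines the study. Relabelling the controls is a minor wording correction.

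**What to change.** Keep the 2.8 recruitment quota and the 2 × 3 group ANOVA. At the end of the primary-aim analysis text, replace the complementary correlation with a named companion analysis for H2 and H3. For each participant, form a tone contrast, for example ascending minus the mean of constant and descending, and regress it on the continuous EDE-Q score. Equivalently, fit a repeated-measures model with tone, EDE-Q and EDE-Q × tone and read off the same contrast; the full interaction also covers unusual patterns across the three tones. Add a quadratic or spline term to check curvature, and report the result beside the group result. Quota sampling on EDE-Q does not bias a correctly specified regression slope on EDE-Q, whereas a correlation coefficient depends on the spread that the quota creates.

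In H1 to H4 and in the study's conclusions, describe controls as below the 2.8 cut-off rather than as without symptomatology.

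The cost is some plan wording and one extra model per outcome on data already collected. The downside is a linearity assumption, limited by the curvature check and the retained ANOVA.

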### Sample size considerations

As these analyses are intended to generate future confirmatory hypotheses, no sample size calculation was conducted. As Jones et al. [53] noted, sample size calculation may be of little value in early exploratory studies where there is a lack of previous research. In an exploratory study, the primary focus is on generating new research questions, identifying patterns and trends, and identifying potential areas for further research, rather than on testing a specific confirmatory hypothesis. As such, the sample size in an exploratory study may not be determined based on statistical power or precision and could be relatively small. Instead, the sample size may be based on the need to obtain a sufficient amount of data to allow for the exploration and identification of meaningful patterns and trends.

In this regard, a total of 100 participants (50 participants in each group) will allow us to gain an exploratory understanding between body perception and non-naturalistic auditory information in participants with subthreshold ED symptomatology. This sample size is the minimum recommended by Brysbaert [54] to seek differences between groups and is also between 30 and 150 participants, that is the sample size usually recommended in exploratory study designs with non-probability sampling [55]. To this end, and based on norms for the Spanish version of the Eating Disorders Examination Questionnaire (S-EDE-Q), we will screen approximately at least 450 young adult females [39].

Due to the limited sample size, we acknowledge that the statistical power for each of the hypotheses proposed in this study to detect differences between groups might not be sufficient according to the traditional standards in experimental psychology (effect size = 0.4, power = 0.80 and alpha value = 0.05) [54]. Therefore, the results should be taken with caution and should be contextualized within an exploratory framework. In case of meaningful results, the present exploratory study will provide the necessary foundation for a formal sample size calculation for a future confirmatory larger-scale study.

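### The whole-sample correlation with EDE-Q depends on the 50/50 quota: r overstates the correlation among eligible screened women and cannot by itself tell a gradient from the group step

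*Protocol article*

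**What the plan says.** Under Participants, women are pre-screened with the S-EDE-Q and enrolled by quota: "The pre-screening will allow to form two groups of similar size", and once one group is full "only participants falling into the other group defined for the study will be invited to take part". Sample size considerations sets 50 per group and adds that "we will screen approximately at least 450 young adult females". Under Statistical analyses, the groups are formed "based on scores falling above or below the cut off of 2.8 on the EDE-Q" and compared by ANOVA. The same section then adds the analysis at issue: "A complementary, secondary correlational analysis will be performed between estimation of body position/size measures and EDE-Q scores considering the entire sample". That sentence names no coefficient and mentions no weighting. Sample size considerations also says that meaningful results will be the basis for a formal sample size calculation for a larger confirmatory study.

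**The concern.** The score that enters the correlation is the score used to select the sample. For a linear relation, selection on the predictor leaves the regression slope unbiased. It changes r, because r depends on the spread of the predictor, and here the quota sets that spread.

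Two consequences follow. First, r is larger than it would be among the eligible women screened. Second, much of the EDE-Q variance is the built-in gap between the groups, so r is driven largely by the contrast that the ANOVA already tests. A correlation offered as a complement to a dichotomised comparison will naturally be read as evidence of a graded relation and of its strength. It may also be carried forward as an effect size for the confirmatory study.

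**Working it through.** **The plan's own figure.** The article states no value for r and makes no sample size calculation, and the norms behind 450 are not shown, so 450 cannot be reproduced. What it implies can be computed. If every high scorer enrols, 50/450 = 11.1% of screened women are at or above 2.8. If three quarters enrol, the share is (50/0.75)/450 = 14.8%. If half enrol, it is (50/0.50)/450 = 22.2%. In the analysed sample the share is 50%.

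**Assumptions.** The EDE-Q distribution is not given. Six shapes were tried: a normal, three gamma shapes truncated at 6 and two beta shapes on 0–6. Each was calibrated to the share above the cut-off. The relation is taken as linear with constant residual variance.

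**Formulas.** D is the difference in mean EDE-Q between the groups.
- Sample variance under 50/50 sampling: V = 0.5·var_high + 0.5·var_low + 0.25·D².
- Variance ratio: k = V / variance among screened women.
- Sample correlation: r = ρ√k / √(1 + ρ²(k − 1)).
- Between-group share of EDE-Q variance: 0.25·D² / V.

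**Example (normal shape, variance 1, 11.1%).** The within-group SDs are 0.42 and 0.83, so the within part is 0.5·0.42² + 0.5·0.83² = 0.43. With k = 1.36 the between part is 0.93, a share of 0.93/1.36 = 0.68. For ρ = 0.30, r = 0.30·√1.36 / √(1 + 0.09·0.36) = 0.344. For the most skewed shape, k = 1.96 and r = 0.30·1.40 / √(1 + 0.09·0.96) = 0.403.

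| Share ≥ 2.8 among screened | k | true 0.20 becomes | true 0.30 becomes | between-group share in sample |
|---|---|---|---|---|
| 11% | 1.36–1.96 | 0.23–0.27 | 0.34–0.40 | 68–78% |
| 15% | 1.25–1.65 | 0.22–0.25 | 0.33–0.38 | 67–77% |
| 22% | 1.14–1.34 | 0.21–0.23 | 0.32–0.34 | 65–76% |

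Without the quota, the between-group share at 11% would be 36–60%.

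**Simulation (8000 studies of 50 + 50, at 11%, normal and one skewed shape).** With a true r of 0.30, the mean sample r was 0.344 and 0.398, and the mean slope was 0.30 for a true 0.30. Spearman moved the same way (0.28 to 0.33, and 0.27 to 0.39). With no association, rejection was 4.7–4.8%. The correlation test and the group t-test correlated 0.80–0.88.

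**Step with no gradient inside groups.** The point-biserial r is d/√(d² + 4), and the expected pooled r is that value times √(between-group share). For d = 0.5 this is 0.243·√0.65 = 0.196 to 0.243·√0.78 = 0.214, with p about 0.05 to 0.03 at n = 100. In simulation such a step gave a significant pooled r in 53–59% of samples, against about 5% for the slope adjusted for group.

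**Effect on a future unselected study.** By Fisher z (two-sided 5%, 80% power), n = (2.80/atanh r)² + 3. A true 0.30 needs 85. Read as 0.34 it gives 66, with actual power about 69%. Read as 0.40 it gives 47, with actual power about 54%.

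**The case against.** The strongest reply is that this is one sentence on a secondary analysis in a study declared exploratory, with convenience sampling and an explicit warning to take results with caution. No hypothesis from H1 to H6 concerns an EDE-Q gradient, and r is nowhere offered as a population estimate. This stands and keeps the point small. The warning, however, concerns limited power against a benchmark ("effect size = 0.4, power = 0.80 and alpha value = 0.05"), not the dependence of r on the quota.

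The size is also uncertain. At 22% high scorers a true 0.30 rises only to 0.32–0.34. At n = 100 the 95% CI for r = 0.30 is about 0.11 to 0.47, wider than any shift shown. Both points stand.

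Three stronger readings are tempting and are not supported:
- A reader might infer that the correlation merely repeats the group test. It does not: 22–35% of the EDE-Q variance is within groups, and if the relation is linear with a true r of 0.20 the pooled test has more power than the split (0.65 against 0.48, normal shape).
- A reader might infer that the 53–59% is a false-positive rate. It is not: a step is a real association with EDE-Q, and the test keeps its level when there is none. The figure shows only that r does not separate a step from a slope. That is true of any pooled correlation, and the quota makes it more pronounced.
- A reader might infer that r is too large for young women in general. The eligibility criteria (BMI 18.5–24.9, no lifetime mental illness, no lifetime under- or overweight, no psychotropic drugs) could narrow the EDE-Q spread and pull r down. The net direction for that wider population is unknown.

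A condensed article may leave within-group reporting to a fuller plan, so its absence is not the point. The point is the stated choice of a whole-sample correlation under an EDE-Q quota.

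**Conclusion.** The point holds as a modest, cheaply mended weakness in a secondary exploratory analysis. Relative to eligible screened women, r is inflated under every EDE-Q shape tried. A true 0.30 appears as about 0.32–0.40, which is 6% too high (0.318/0.30) at the low end and 34% (0.403/0.30) at the high end. This rests on assumed EDE-Q distributions, on 11–22% high scorers and on a linear relation. Because 65–78% of the EDE-Q variance is the group gap, a significant pooled r cannot by itself distinguish a graded relation from a step. No primary comparison is affected.

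**What to change.** Replace the correlation as the main estimate by a regression of each perception measure on EDE-Q, reporting the slope per EDE-Q point with its 95% CI. Selection on EDE-Q does not bias this slope if the relation is linear. Add the slope with group in the model as a check for a within-group gradient, and say that it is weak: for a true r of 0.20 its power is roughly 0.2–0.3, against about 0.6–0.8 for the pooled test. A null result there is not evidence against a gradient.

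If r is quoted, either label it as specific to the 50/50 sample or reweight the groups to their fractions among the women screened. Do not use the unweighted r to size a future unselected study.

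The cost is analysis wording and keeping the screening counts; no new data are needed. Reweighting loses precision. At 11% the weights are 0.111/0.5 = 0.222 and 0.889/0.5 = 1.778, so the effective sample is 100² / [50·(0.222² + 1.778²)] = about 62 of 100.
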